### 2.8. Oral Sweet Solution

The oral glucose solution will be a 30% glucose solution (Glux® from Pharma Stulln, Germany), which each patient in the GG will receive within 30 seconds, 150 seconds before the intervention. The application and dosage of the oral glucose solution during minor painful interventions are based on the Austrian interdisciplinary guidelines for perioperative pain management [23]. A dosage of 0.2 ml/kg body weight is recommended.

### 2.9. The Acupuncture Point

LI 4 is called in Chinese “He Gu,” which means “Union Valley.” LI 4 is located on the dorsal side of the hand in the middle between 1st and 2nd metacarpal bones, in direction to the middle of the 2nd metacarpal bone. This acupuncture point is one of the most frequently used points in acupuncture and is the main point against any kind of pain.

The acupuncture point is described following the standard of international acupuncture nomenclature [24]. In addition, the acupuncture treatment is described according to the established guidelines of STandards for Reporting Interventions in Clinical Trials of Acupuncture (STRICTA) [25].

### 2.10. Technical Parameters of Laser Acupuncture

The AG will receive laser acupuncture using LABpen MED 10 (Behounek, Graz, Austria). This Laser is a continuous wave semiconductor GaAs (Gallium Arsenide) laser with wavelength of 675 nm and output power of 10 mW, with diameter 1.5 mm [26].

The body acupuncture point LI 4 will be treated for 60 seconds per point, in total 120 seconds (=0.6 J/point, which corresponds to an energy dosage of 34 J/cm^2^) [27].

### 2.11. Safety Precautions during Laser Acupuncture

The new classification for low-level lasers according to the European Norm (EN 60825-1) is 3R, which means that radiation can cause serious eye damage [26].

Therefore, the use of protective glasses to avoid retinal damage is necessary. The acupuncturist and any other person in the treatment room will wear specific protective glasses. All included neonates will wear an eye protector (Natus Biliband Eye Protector, Natus Medical, San Carlos, California), which is routinely used in neonates during phototherapy for neonatal jaundice [28], on the one hand to avoid eye damage in neonates who receive laser acupuncture and on the other hand to manipulate all participants in both groups equally. The eye protector will be removed 30 seconds before heel lance.

The Department of Technical and Organisational Safety of the Medical University of Graz has examined and approved the effectiveness of this eye protector and application of the low-level laser.

### 2.12. Allocation and Randomisation

Neonates will be randomly allocated to laser acupuncture or orally administered glucose solution in a 1 : 1 ratio using an online software program for clinical trials (https://www.randomizer.at) developed at the Medical University of Graz. Just before the intervention, the included participant's code and sex will be typed in by the principal investigator and the program will show the allocation of this participant. Therefore the principal investigator will only know the allocation of this and the previous included neonates; the allocation of any upcoming participants will not be visible. Only the biometrician knows the used randomisation algorithm. If a neonate has to be excluded after randomisation, the reason for revision of randomisation will be documented within the program. This revision can only be done by the biometrician. Randomisation will not be stratified for any factor.

### 2.13. Blinding

The blinding will be “observer blinded,” due to the fact that the video recordings will be analysed by a skilled paediatric nurse, who will know neither the participant nor the intervention. To guarantee blinding, these video recordings will show only 15 seconds before the heel lance and the blood sampling. The interventions with laser acupuncture or oral glucose solution will not be recorded.

### 2.14. Data Management

Pseudonymous data will be recorded first on a Case Report Form and then on an Excel Sheet (Microsoft Excel 2010, Microsoft Corporation, Redmond, Washington, USA) for statistical analysis including data from the neonate, the mother, and the delivery, as well as information recorded during the intervention. Outcome parameters will be collected before and during intervention (e.g., heart frequency, oxygen saturation) and on the basis of video recordings of the participants (e.g., crying duration, PIPP). Adverse events will be collected and reported during the intervention and supervised by a paediatrician. However, from preliminary trials, little to no risk for adverse events is expected for the included neonates. If there will be suspicion of adverse events or harm in most cases, discontinuing or modifying allocated interventions for given trial participants will be reviewed. Furthermore, interim analyses will not be performed.

Data will be stored on restricted-access files at the Division of Neonatology, except for the study contributors.

### 2.15. Sample Size

In a group of neonates receiving laser acupuncture, Gottschling et al. reported a pain reaction following heel lance of 6.4 ± 1.9 in PIPP score [13]. Assuming a SD (standard deviation) of 1.9 in pain scores of neonates undergoing heel lance, a sample size of 95 neonates will have a power of 80% (one-sided *t*-test) to reject the null hypothesis that the laser acupuncture and oral glucose administration are not equivalent (the difference in means, *μ*AG  −  *μ*GG, is 1.0 or farther from zero in the same direction) in favour of the alternative hypothesis that the means of the two groups are equivalent, assuming that the expected difference in means is 0. Assuming a minimal dropout of *n* = 5 neonates, we expect to include 95 participants in total.

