### 2.16. Statistical Analysis

We will compare the PIPP scores of both groups using intention-to-treat analysis (ITT). Furthermore, per-protocol (PP) analysis will be performed, since ITT analysis increases the chance of finding noninferiority (increase of type I error) [29]. Results of ITT and PP analysis will be compared.

First baseline characteristics of both groups (gestational age, sex, APGAR score, birth weight, birth size, head circumference, birth mode, and day of life at the time of heel lance) will be compared using *t*-test or Mann–Whitney *U* test for continuous variables and chi-square test or Fisher's exact test as appropriate. For differences in these characteristics, further analysis will be adjusted.

Laser acupuncture will be considered noninferior to oral glucose administration, if the upper boundary of the two-sided 95% confidence interval (CI) for the mean difference between laser acupuncture and oral glucose administration will be less than the margin, *δ* = 1. If data will not be normally distributed, nonparametric tests will be applied.

For ITT analysis, missing primary outcome measures will be imputed by using multiple imputations. For PP analysis, no imputations will be performed. Secondary outcomes will be compared using *t*-test or Mann–Whitney *U* test for continuous variables and chi-square test or Fisher's exact test as appropriate. Since interventions will be of short duration and no risks are associated with the intervention, no interim analysis will be performed.

The used statistic programs for statistical analysis will be IBM SPSS Statistics (Statistical Package for the Social Sciences) and SAS (state-of-the-art statistical analysis software).

The primary outcome measure is the PIPP score as defined above.

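### The stated 80% power corresponds to a one-sided 5% test; under the two-sided 95% confidence interval rule the trial will apply, power is about 70%

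*Protocol article*

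**What the plan says.** Section 2.15 (Sample Size) sets out the calculation. The SD is fixed by "Assuming a SD (standard deviation) of 1.9 in pain scores of neonates undergoing heel lance", the margin is 1.0 PIPP point, and the true effect is set by "assuming that the expected difference in means is 0". The test is a one-sided t-test, with no significance level given. On these inputs, "a sample size of 95 neonates will have a power of 80" percent. The last sentence allows for 5 dropouts and ends "we expect to include 95 participants in total". The null is to be rejected "in favour of the alternative hypothesis that the means of the two groups are equivalent".

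Section 2.16 (Statistical Analysis) gives the decision rule. Laser acupuncture is noninferior "if the upper boundary of the two-sided 95% confidence interval (CI) for the mean difference" between laser and glucose "will be less than the margin, *δ* = 1". Section 2.1 also describes the trial as a noninferiority design.

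**The concern.** A noninferiority claim based on the upper limit of a two-sided 95% interval is a one-sided test at 2.5%. A calculation labelled one-sided, with no alpha, invites the question whether it used 5%. If it did, the power in section 2.15 belongs to an easier test than the one in section 2.16.

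This affects the primary outcome and the trial's only confirmatory claim. Ethics reviewers and readers take the 80% as the chance that the trial succeeds if laser is as good as glucose. If the true chance is lower, an inconclusive result is more likely than disclosed and can be mistaken for evidence that laser is worse. The mismatch also leaves two success criteria in view: the 95% interval in the text and the 90% interval implied by the sizing. A result whose upper limit passes one and fails the other would be disputed.

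Two smaller defects sit in the same paragraph. The number 95 is given both as the sample that yields the power and as the sample after allowing for dropouts. The hypotheses are also worded as equivalence, although a one-sided test cannot support that conclusion.

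**Working it through.** **Inputs.** SD 1.9, margin 1.0, true difference 0, power 80%, total 95 and 5 dropouts come from section 2.15. The 1:1 allocation comes from section 2.12 and the 95% interval rule from section 2.16. Alpha is not printed for the sample size, so it is solved for.

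**Step 1: reproduce the stated sample size.** With a true difference of 0, the normal approximation is

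n per arm = 2 × (z for 1 − alpha + z for power)² × SD² / margin²

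- One-sided 0.05: 2 × (1.645 + 0.842)² × 3.61 / 1 = 44.6, so 45 per arm. Then 90 + 5 = 95, which is the stated total.
- One-sided 0.025: 2 × (1.960 + 0.842)² × 3.61 / 1 = 56.7, so 57 per arm or 114 in total, which does not match.
- Equivalence by two one-sided tests at 5% each: about 62 per arm, which does not match.
- Reading 95 as the number per arm gives 97.6% power at 0.05 and 95.0% at 0.025, which does not match either.

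**Step 2: power for the t-test that section 2.15 names.** The standard error is 1.9 × √(1/n₁ + 1/n₂). For 45 and 45 it is 0.4006, giving a noncentrality of 1/0.4006 = 2.50. For 47 and 48 it is 0.3899, giving 2.56. Power is the probability that a noncentral t exceeds the critical value.

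| Evaluable | One-sided 0.05 | One-sided 0.025 (section 2.16 rule) |
|---|---|---|
| 90 (45/45) | 79.7% | 69.5% |
| 95 (47/48) | 81.6% | 71.9% |

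The normal approximation gives 80.3% and 70.4% for 90 neonates, and 82.1% and 72.7% for 95.

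**Step 3: solve for alpha.** The level that gives exactly 80% by the t-test is 0.051 with 90 neonates and 0.044 with 95. Neither is near 0.025.

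**Step 4: what the rule demands of the data.** With 90 evaluable and an observed SD of 1.9, the upper limit is below 1 only if the observed difference is below 1 − 1.987 × 0.4006 = 0.20 points. At one-sided 5% the threshold would be 1 − 1.662 × 0.4006 = 0.33 points.

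**Step 5: size needed for 80% under section 2.16.** This takes 57 per arm (114) by the normal approximation or 58 per arm (116) by the t-test. Adding the same 5 dropouts gives 119 to 121 randomised.

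**The case against.** Several points can be made for the plan.

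- **The 5% level is inferred.** Section 2.15 prints no alpha, and with the t-test 45 per arm gives 79.7%, so strictly 46 per arm would be needed. The split into 90 evaluable plus 5 is likely but not documented. This stands as a caveat and the sponsor should confirm it. It does not rescue the 80%: whatever alpha was used, the section 2.16 rule gives about 70% to 72% on the plan's own assumptions.
- **About 70% is the less favourable case.** The intention-to-treat analysis imputes missing outcomes, so 95 neonates enter it. The 71.9% applies only if no outcome is missing, since imputation does not fully restore lost information. The fair range is 69.5% to 71.9%.
- **The equivalence wording is loose rather than a different test.** The parenthesis in section 2.15 already describes a null in one direction, and sections 2.1 and 2.16 speak of noninferiority. No two one-sided tests procedure is planned, so its power is not part of this finding. The wording still needs correcting, because the Conclusion hypothesises that laser reduces pain equally to glucose.
- **Type I error is not inflated.** This is correct. The interval rule is the stricter of the two, and a positive result would be valid at one-sided 2.5%. The harm is a misstated power and a higher chance of an inconclusive trial. That an inconclusive result would be misread is a risk, not something the plan announces.

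**Conclusion.** The concern holds. The power figure in section 2.15 and the decision rule in section 2.16 cannot both be right. On the plan's own inputs (SD 1.9, margin 1.0, true difference 0, 1:1 allocation), power for the stated rule is 69.5% with 90 evaluable neonates and 71.9% with 95, a shortfall of roughly 8 to 10 percentage points. The risk of missing noninferiority is 28% to 31% instead of 20%.

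That the sizing used one-sided 5% is a back-calculation, and it is the only standard variant tried that returns both 95 and 80%. The shortfall does not depend on that inference. The calculation itself is sound at 5%; the error is that it was made for a different test from the one that decides the trial. The double use of 95 moves power by only about 2 points, and the equivalence wording moves it not at all. Both should be corrected in the same edit.

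**What to change.** Keep the two-sided 95% interval rule and bring section 2.15 into line with it. Suggested text, once the sponsor confirms the split:

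> With 90 evaluable neonates (45 per arm; 95 randomised, allowing for 5 dropouts), SD 1.9, margin 1.0 and a true difference of 0, power is about 70% at one-sided alpha 0.025. The hypotheses are H0: μAG − μGG ≥ 1.0 versus H1: μAG − μGG < 1.0.

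Remove the equivalence wording from the hypotheses.

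This is a change of text only. It needs no additional neonates, and its cost is a less favourable stated power. If 80% is to be kept and recruitment is still open, the alternative is 114 to 116 evaluable neonates, or 119 to 121 randomised. Section 2.1 has data collection ending in 2016, so that option may no longer exist. The success criterion should not be relaxed to a 90% interval to match the sizing once data have been seen.

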### 2.16. Statistical Analysis

We will compare the PIPP scores of both groups using intention-to-treat analysis (ITT). Furthermore, per-protocol (PP) analysis will be performed, since ITT analysis increases the chance of finding noninferiority (increase of type I error) [29]. Results of ITT and PP analysis will be compared.

First baseline characteristics of both groups (gestational age, sex, APGAR score, birth weight, birth size, head circumference, birth mode, and day of life at the time of heel lance) will be compared using *t*-test or Mann–Whitney *U* test for continuous variables and chi-square test or Fisher's exact test as appropriate. For differences in these characteristics, further analysis will be adjusted.

Laser acupuncture will be considered noninferior to oral glucose administration, if the upper boundary of the two-sided 95% confidence interval (CI) for the mean difference between laser acupuncture and oral glucose administration will be less than the margin, *δ* = 1. If data will not be normally distributed, nonparametric tests will be applied.

For ITT analysis, missing primary outcome measures will be imputed by using multiple imputations. For PP analysis, no imputations will be performed. Secondary outcomes will be compared using *t*-test or Mann–Whitney *U* test for continuous variables and chi-square test or Fisher's exact test as appropriate. Since interventions will be of short duration and no risks are associated with the intervention, no interim analysis will be performed.

The used statistic programs for statistical analysis will be IBM SPSS Statistics (Statistical Package for the Social Sciences) and SAS (state-of-the-art statistical analysis software).

The primary outcome measure is the PIPP score as defined above.

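### The noninferiority rule names no analysis set, so the per-protocol analysis added to guard against ITT inflation places no condition on the claim

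*Protocol article*

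**What the plan says.** All the statements that matter stand in section 2.16 of the protocol article.

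- ITT is named first: "We will compare the PIPP scores of both groups using intention-to-treat analysis (ITT".
- PP is added with a reason: "since ITT analysis increases the chance of finding noninferiority (increase of type I error".
- The link between the two is one sentence: "Results of ITT and PP analysis will be compared".
- The decision rule comes later and mentions neither set: "Laser acupuncture will be considered noninferior to oral glucose administration, if the upper boundary" of the two-sided 95% interval for the mean difference "will be less than the margin, *δ* = 1".
- Missing data are treated differently in the two sets: "For ITT analysis, missing primary outcome measures will be imputed by using multiple imputations", whereas "For PP analysis, no imputations will be performed".

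The article nowhere says that PP is the primary set, that both sets must meet the margin, or how to read a disagreement.

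Other sections show that the sets can differ. Section 2.12 allows exclusion after randomisation, section 2.14 allows an allocated intervention to be stopped or modified, and section 2.15 allows for 5 dropouts.

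**The concern.** In a noninferiority comparison, neonates who do not receive their allocated treatment as intended tend to pull the arms together. If laser acupuncture is truly worse by the margin, that dilution makes a false claim more likely on ITT. The plan recognises this and gives it as the reason for the PP analysis.

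A safeguard works only if it can stop the claim. Comparing two results does not say what happens when ITT has an upper limit below 1 and PP does not. In that case the printed rule is met on the analysis the plan itself describes as too lenient. The opposite case, PP passing and ITT failing, has no prespecified reading either. The headline conclusion could then depend on a choice made after the results are known.

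**Working it through.** **Inputs.** Margin 1 and two-sided 95% interval (one-sided 0.025): section 2.16. SD 1.9, expected difference 0, total 95, 80% power, 5 dropouts: section 2.15. Allocation 1:1: section 2.12. My assumptions: 47 laser and 48 glucose neonates; k laser-arm neonates with glucose-like outcomes; PP removes exactly those k; deviation is unrelated to the neonate's pain response.

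**Step 1: the plan's own figure.** Section 2.15 gives no alpha. At one-sided 0.05, n per arm = 2 × 1.9² × (1.645 + 0.842)² / 1² = 44.7, so 45 per arm. That is 90 in total, and 90 + 5 = 95. The stated size reproduces, so the inputs are read correctly. At the one-sided 0.025 implied by the two-sided 95% interval, 95 neonates give power of 71.8% (exact noncentral t). That is a separate matter, but it is the starting point for the cost in step 4.

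**Step 2: ITT dilution at the margin.**

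- SE = 1.9 × √(1/47 + 1/48) = 0.390; 93 degrees of freedom; critical t = 1.986.
- If the true difference is 1.0, the ITT difference is 1 − k/47.
- The noncentrality is (1 − ITT difference) / SE = (k/47) / 0.390.

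| k | ITT difference | Noncentrality | P(upper limit < 1) |
|---|---|---|---|
| 0 | 1.000 | 0 | 2.5% |
| 1 | 0.979 | 0.055 | 2.8% |
| 2 | 0.957 | 0.109 | 3.2% |
| 5 | 0.894 | 0.273 | 4.6% |
| 9 | 0.809 | 0.491 | 7.0% |

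**Step 3: simulation of the possible rules at a true difference of 1.0** (pooled t interval, 400,000 runs per row). Mixed outcomes widen the laser arm's spread slightly, so the ITT rates at k = 5 and 9 are a little below the formula.

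| k | ITT alone | PP alone | Either set | Both sets |
|---|---|---|---|---|
| 1 | 2.8% | 2.5% | 3.0% | 2.4% |
| 2 | 3.2% | 2.5% | 3.3% | 2.4% |
| 5 | 4.4% | 2.5% | 4.5% | 2.4% |
| 9 | 6.7% | 2.5% | 6.8% | 2.4% |

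Passing on either set adds about 0.1 percentage point to ITT alone. The excess over 2.5% is almost entirely ITT dilution. Spreading deviations over both arms gives much the same result: ITT alone passes 4.3% of the time with 5 crossovers in total and 7.2% with 10.

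**Step 4: price of requiring both sets, at a true difference of 0.**

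| k | Power, ITT alone | Power, both sets | Sets disagree |
|---|---|---|---|
| 1 | 72% | 70% | 2.9% |
| 2 | 72% | 69% | 4.2% |
| 5 | 72% | 67% | 7.0% |
| 9 | 72% | 64% | 10.3% |

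The last column shows that disagreement also occurs when the treatments are truly equal, so a rule for it is needed in either case.

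**The case against.** Four points can be made against this.

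1. **The text states no either-set rule.** A reader might infer that the plan grants two chances to pass. It does not say so. Naming ITT first and adding PP out of concern about ITT can be read as a main analysis with a cautious check. This stands: the plan leaves an ITT-only claim possible but does not announce one. The second look would also add almost nothing to the error.

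2. **Deviation is likely to be rare.** The intervention is a single 150-second procedure, carried out by a doctor following written procedures (section 2.4), with allocation revealed just beforehand (section 2.12). The 5 dropouts of section 2.15 are not crossovers; missing outcomes are imputed under ITT and need not shrink the difference. This also stands. A reader tempted by the rows for 5 or 9 neonates should know that nothing in the document supports rates of that order.

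3. **Such detail often sits in an analysis plan.** This holds only in part. The article itself prints the decision criterion, both sets, the imputation rule for each and the reason for PP. It leaves open only which set the criterion applies to, so the printed rule is incomplete on the very point the plan raises.

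4. **PP can be biased either way by exclusions after randomisation.** True, and it argues for requiring both sets rather than moving the decision to PP alone.

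**Conclusion.** The point holds as a defect in the decision rule. The plan identifies a type I error problem with ITT and offers PP as the answer, but it does not make the claim depend on PP. As written, noninferiority could be declared on ITT when PP fails.

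The likely effect is modest: about 3% instead of 2.5% with 1 or 2 deviating neonates, rising to 4.4% with 5 and 6.7% with 9. These figures rest on an SD of 1.9, a true difference equal to the margin and assumed numbers of glucose-like outcomes in the laser arm. With no deviations and no missing scores, the rate is 2.5% under any of the rules.

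It would go too far to say that the false noninferiority rate is uncontrolled, that the trial will rest its conclusion on ITT, or that two looks are the source of the inflation. The document supports none of these. The change is worth making because it is cheap and closes the gap the plan itself points to.

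**What to change.** Add one sentence to section 2.16 before any unblinded analysis:

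*Noninferiority is concluded only if the upper limit of the two-sided 95% CI is below 1 in both the ITT and the PP set; if they disagree, noninferiority is not shown.*

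Under the assumptions above this holds the false noninferiority rate at about 2.4%. It needs no new data. The cost is power: at a true difference of 0, from about 72% on ITT to 69–70% with 1 or 2 deviations and 67% with 5. The loss is zero if the two sets coincide.

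### Adjustment covariates are chosen by significance tests of baseline differences, so it is not fixed in advance whether the interval that decides noninferiority is adjusted

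*Protocol article*

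**What the plan says.** Section 2.16 sets an order of work. It opens with "First baseline characteristics of both groups", namely "gestational age, sex, APGAR score, birth weight, birth size, head circumference, birth mode, and day of life at the time of heel lance": eight characteristics. The comparison uses a t-test or Mann–Whitney test for continuous variables, and a chi-square or Fisher test otherwise. The consequence is then stated: "For differences in these characteristics, further analysis will be adjusted". No significance level or other threshold for a difference is given.

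The next paragraph gives the decision rule. Its criterion, introduced by "if the upper boundary of the two-sided 95% confidence interval (CI) for the mean difference between laser acupuncture and oral glucose administration", is that this limit lies below 1 PIPP point. The text does not say whether this difference is adjusted, and it does not exempt the primary comparison from the adjustment rule.

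No design factor fixes a covariate either. Section 2.12 says: "Randomisation will not be stratified for any factor".

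**The concern.** The rule has three weaknesses.

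- In a randomised trial the baseline null hypothesis is true by design. A significant test therefore detects a chance imbalance and nothing else.
- What makes a covariate worth adjusting for is its relation to PIPP, and the baseline test carries no information on that. A strongly prognostic covariate is left out when it happens to be balanced, and an irrelevant one is included when it happens not to be.
- The noninferiority verdict rests on one confidence limit. If the model behind that limit depends on which baseline tests happen to be significant, and the text does not say whether the adjusted or the unadjusted limit decides, the primary analysis is not fixed before the data are seen.

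**Working it through.** **Inputs from the documents.** SD 1.9, true difference 0, margin 1.0, power 80%, 95 neonates including 5 dropouts (section 2.15); 1:1 allocation (section 2.12); eight tested characteristics and a two-sided 95% interval (section 2.16).

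**Assumptions, because the documents are silent.** Baseline tests at 5% (10% also shown); covariate R² for PIPP of 0.05 to 0.5; correlation among covariates of 0 or 0.3.

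**1. The plan's own sample size.** At one-sided 5%, n per arm = 2 × 1.9² × (1.645 + 0.842)² / 1² = 44.6, so 45. That is 90 in total, or 95 with 5 dropouts, as stated. The two-sided 95% interval corresponds to one-sided 2.5%, which would need 2 × 1.9² × (1.960 + 0.842)² = 56.7, so 57 per arm or 114. That mismatch is a separate matter. It matters here only because it explains why unadjusted power at 90 is about 70%.

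**2. How often the rule triggers adjustment.** With eight independent tests, 1 − 0.95⁸ = 33.7% at the 5% level and 1 − 0.90⁸ = 57.0% at 10%. With correlation 0.3, simulation gives about 30% at 5%.

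**3. How close the verdict sits to the threshold.** With 45 per arm the half-width is 1.987 × 1.9 × √(2/45) = 0.796. The observed difference must therefore be below 1 − 0.796 = 0.204. A covariate that is just significant at 5% is imbalanced by 1.987 × √(2/45) = 0.42 SD. If its correlation with PIPP is r, adjustment moves the estimate by about 0.42 × 1.9 × r = 0.80r points. A shift of 0.1 to 0.2 points thus needs r of about 0.13 to 0.25. The documents give no r, so this is an illustration.

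**4. Simulation.** 45 per arm, eight normally distributed covariates with equal effects, 8,000 runs per scenario, noninferiority declared if the upper 95% limit is below 1. The prespecified model contains all eight covariates. Entries are percentages.

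| R² | Corr. | Any test significant | Verdicts differ, selected vs unadjusted (true diff. 0) | Power unadjusted | Power selected | Power prespecified | One-sided error, selected (true diff. 1) |
|---|---|---|---|---|---|---|---|
| 0.05 | 0 | 34 | 3.1 | 69 | 68 | 67 | 2.5 |
| 0.05 | 0.3 | 29 | 3.8 | 70 | 70 | 68 | 2.8 |
| 0.1 | 0 | 34 | 3.7 | 70 | 69 | 70 | 2.6 |
| 0.1 | 0.3 | 30 | 6.0 | 70 | 70 | 70 | 2.4 |
| 0.3 | 0 | 33 | 5.4 | 70 | 70 | 80 | 2.1 |
| 0.3 | 0.3 | 30 | 10.1 | 69 | 71 | 80 | 1.7 |
| 0.5 | 0 | 33 | 7.1 | 69 | 70 | 91 | 1.8 |
| 0.5 | 0.3 | 30 | 11.4 | 69 | 74 | 91 | 1.3 |

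The Monte Carlo standard error of the error rate is √(0.025 × 0.975 / 8000) = 0.17 percentage points. The 2.8% entry is therefore compatible with 2.5%, and the unadjusted analysis gave 2.9% in the same runs. At a true difference of 1, verdicts differ in about 1–2% of trials.

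**The case against.** **Selection looks only at baseline.** The candidates and the tests are listed in advance, and PIPP plays no part in choosing covariates. Followed literally, the rule gives one interval per dataset. This stands in part. It does not apply in full because no threshold for a difference is given and the decision rule does not say which mean difference it uses.

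**The adjusted analysis may be supplementary.** The sentence speaks of further analysis, after the ITT and PP comparisons have been introduced. That reading is possible. But the sentence comes before the decision rule and makes no exception for it, so the text cannot settle the question.

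**This is detail for an analysis plan.** A missing threshold alone would be. Here the protocol states a selection rule, and a plan that followed it would inherit the weakness.

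A reader might also infer more than the documents support:

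- *That the rule inflates type I error.* It does not. The selected model's one-sided error is at nominal or below it within simulation error, and falls to 1.3% when covariates are strongly prognostic. Even freedom to report whichever of the two models succeeds gives only about 2.6–3.3%.
- *That 34% is a rate of harm.* It is the rate at which adjustment is triggered, under independence and an assumed level. Birth weight, birth size, head circumference and gestational age are likely to be correlated, which lowers it. A trigger matters only if the flagged covariate predicts PIPP.
- *That precision is generally lost.* Nothing in the article shows that any of the eight characteristics predicts PIPP in healthy term neonates. At R² of 0.1 or below, prespecified adjustment gains nothing, and with all eight covariates at R² 0.05 it costs a little.
- *That unstratified randomisation is a fault.* It is a legitimate choice. It means only that no stratification factor supplies a covariate.

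**Conclusion.** The point holds as a weakness in prespecification. The stated rule lets chance baseline imbalance choose the covariates, and the article does not say whether the interval compared with the margin of 1 is adjusted. On an assumed 5% level the model changes in about 30–34% of trials. The choice between the test-selected and the unadjusted interval alters the verdict in about 4–11% of trials at a true difference of 0 for assumed R² of 0.1–0.5, and in 3–4% at R² 0.05.

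Error control is not the problem, because the rule tends to be conservative. The power loss is conditional: it appears at R² of about 0.3 or more, where the selected model has about 70–71% power against 80% for prespecified ANCOVA. The documents give no R², so the size of that loss is unknown. The rule should be changed, but it does not by itself invalidate the trial.

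**What to change.** In section 2.16:

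- Delete the baseline significance tests and the sentence on adjusting for differences. Present the eight characteristics descriptively by arm.
- Name one primary model before PIPP scores are linked to allocation, to be used whatever the observed imbalance. If some of the collected characteristics are expected to predict PIPP, use ANCOVA of PIPP on treatment plus a short list of them, each with its reason. If none is, use the unadjusted difference.
- State that the 95% interval from this model, and no other, is compared with the margin of 1. Report the other analysis as a sensitivity analysis.

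Choose covariates by expected prognostic value. Gestational age needs particular thought: only term neonates are enrolled, and the maxima in section 2.7 (21 points below 28 weeks, 18 at term) imply that the PIPP gestational-age item adds nothing at term.

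The cost is a change of wording and, with ANCOVA, 2–3 degrees of freedom. No new data are needed, and this change does not alter the sample size.
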